#### Control

The control group are given general information about lifestyle and diabetes risk. This is achieved individually (15 minutes), and some printed material is delivered; with the message to reduce weight and increase physical activity levels.

### Outcome measures

The primary outcome measure in the study is the change in insulin sensitivity. Insulin sensitivity will be estimated from the 3 hour oral glucose tolerance test. First, the change in the area under the curve for glucose divided by the change in the area under the curve for insulin will be used. Secondly, the Homeostatic Model for Insulin Resistance [25] will be used. Finally, an estimate of insulin sensitivity will be derived from the index proposed by Matsuda and DeFronzo [26], which is calculated according to the following formula:$$ \frac{10,000}{\sqrt{\mathrm{fasting}\kern0.5em \mathrm{glucose}\kern0.5em \left[\mathrm{mg}/\mathrm{dl}\right]\times \mathrm{fasting}\kern0.5em \mathrm{insulin}\kern0.5em \left[\mathrm{mU}/\mathrm{ml}\right]\times \mathrm{mean}\kern0.5em \mathrm{glucose}\kern0.5em \left[\mathrm{mg}/\mathrm{dl}\right]\times \mathrm{mean}\kern0.5em \mathrm{insulin}\kern0.5em \left[\mathrm{mU}/\mathrm{ml}\right]}} $$

Secondary outcomes will also be measured at baseline and follow-up namely: 2 hour postprandial blood glucose on a 75 g oral glucose tolerance test, maximal fitness levels, body composition and anthropometric measures, lipid profile, blood pressure, heart rate variability, dietary adherence and free-living physical activity levels. Participants will also complete a number of self-reported surveys relating to quality of life, self-efficacy and barriers and facilitators to exercise participation. Additional file 1 outlines the definitions and measurement techniques relating to all outcome measures employed.

### Analysis plan

At follow-up (13–14 weeks post-baseline assessment) all participants will undergo the same biomedical, anthropometric and psychological measures administered at baseline. At the end of the study, data will be cleaned and checked for normality and transformed as needed. Two-tailed *t* tests, analysis of covariance (ANCOVA) and multiple linear regression models will be applied to compare between-group and within-group changes in means before and after intervention for primary and secondary outcome measures. Analysis and reporting will be in line with the Consolidated Standards of Reporting Trials (CONSORT) guidelines; primary analyses will be conducted on an intention-to-treat basis.

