### Sample size and power calculation

A 3:1 ratio will be used to randomize a total of 360 participants; 270 to the intervention group and 90 to the control group. We expect a 10 % attrition rate, which will leave 243 and 81 participants in the intervention and control groups, respectively. Based on the effect of lifestyle intervention on insulin sensitivity reported in a previous study [25], we have calculated that, with this sample size and with a power of 0.8, it will be possible to detect a 17 % (equivalent to 0.36 standard deviation) difference in insulin sensitivity between the intervention group and the control group in this study.

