### Randomization process

An allocation sequence is obtained using the RALLOC command implemented in the statistical software package STATA/IC 12.1 (StataCorp LP, USA) and used to randomize eligible participants in a 3:1 ratio to intervention (DEXLIFE ‘self-selected’ lifestyle programme) or control. Randomization is stratified by age, sex and body mass index using random blocks of four, to ensure a balance of participant characteristics in each group. Participants will be randomly allocated to either intervention or control by the project manager according to the allocation sequence. Because of the nature of the intervention, neither the participants nor the research team are blinded to allocation.

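### The analysis plan lists t tests, ANCOVA and regression for the primary outcome but does not say which decides; naming one baseline- and strata-adjusted ANCOVA would settle this and gain precision without extra participants

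*Protocol article*

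**What the plan says.** The hypothesis (protocol article, Hypothesis) is single and between-group: mean change in insulin sensitivity will rise more under the intervention than under control. Outcome measures agrees: "The primary outcome measure in the study is the change in insulin sensitivity".

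The Analysis plan gives one sentence on methods. It opens with "Two-tailed *t* tests" and goes on: "analysis of covariance (ANCOVA) and multiple linear regression models will be applied to compare". The comparisons it has in view are of both kinds, between the arms and within each arm, and it gives their scope as "changes in means before and after intervention for primary and secondary outcome measures". It calls the primary analyses intention-to-treat, but says neither which method is the primary analysis nor what covariates enter the ANCOVA or the regressions.

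Randomization process states: "Randomization is stratified by age, sex and body mass index using random blocks of four". The Analysis plan does not return to these factors.

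Sample size and power calculation claims, "with this sample size and with a power of 0.8", the ability to detect a 17% difference ("equivalent to 0.36 standard deviation) difference in insulin sensitivity between the intervention group and the control group"). It does not say whether this is the SD of the change or of the value at one visit.

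**The concern.** One hypothesis needs one deciding test. The article does not simply leave the matter for later: it commits several methods to the primary outcome and ranks none of them. Two things follow.

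- **Error control.** A t test on change and a baseline-adjusted ANCOVA can fall on opposite sides of 0.05 in the same data. If the choice can be made after the results are seen, the chance of a false positive exceeds the nominal level. The research team is not blinded to allocation, so the choice should not be left open.
- **Precision.** With equal variances at the two visits, ANCOVA on the baseline value is never less efficient than a t test on change, apart from one degree of freedom, and is often clearly better. The baseline value, age, sex and BMI are all known before randomization. A primary analysis that ignores them makes less use of the same participants.

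**Working it through.** **Inputs from the protocol article.** Analysed numbers 243 and 81 (360 randomized 3:1, 10% attrition), difference 0.36 SD, power 0.8, two-tailed tests.

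**Assumptions, because the article gives no figure.** Two-sided alpha 0.05; equal variances at baseline and follow-up; baseline-to-follow-up correlation r of 0.3, 0.5, 0.7 and 0.9.

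**Step 1: the plan's own figure.** The standard error of a difference in means, in SD units, is √(1/243 + 1/81) = 0.1283. The noncentrality is 0.36 / 0.1283 = 2.806. Power is 0.799 from the noncentral t distribution and 0.801 from the normal approximation. The stated 0.8 is therefore reproduced by an unadjusted two-sample comparison. A one-sided test would give 0.877 and does not match.

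**Step 2: change-score t test against ANCOVA.** With level variance 1:

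- variance of the change: 2(1 − r)
- residual variance of ANCOVA on baseline: 1 − r²
- ratio of ANCOVA to change score: (1 − r²) / [2(1 − r)] = (1 + r)/2, which is below 1 for every r below 1.

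The article does not say which SD the 0.36 refers to, so both readings are shown.

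*Reading A, 0.36 in SDs of change.* The t test has SD 1 and power 0.80 at every r. The ANCOVA residual SD is √((1 + r)/2).

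*Reading B, 0.36 in SDs of the level.* The t test on change has SD √(2(1 − r)). The ANCOVA residual SD is √(1 − r²).

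| r | A: ANCOVA SD | A: t test power | A: ANCOVA power | B: change SD | B: ANCOVA SD | B: t test power | B: ANCOVA power |
|---|---|---|---|---|---|---|---|
| 0.3 | 0.806 | 0.80 | 0.93 | 1.183 | 0.954 | 0.66 | 0.83 |
| 0.5 | 0.866 | 0.80 | 0.90 | 1.000 | 0.866 | 0.80 | 0.90 |
| 0.7 | 0.922 | 0.80 | 0.86 | 0.775 | 0.714 | 0.95 | 0.97 |
| 0.9 | 0.975 | 0.80 | 0.82 | 0.447 | 0.436 | about 1.00 | about 1.00 |

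Worked entry, reading A, r = 0.5: noncentrality 0.36 / (0.866 × 0.1283) = 3.24, power 0.90. The detectable difference at power 0.80 falls from 0.36 to about 0.31 SD (0.36 × 0.866). Any further gain from age, sex and BMI cannot be computed from the article.

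**Step 3: type I error if either test may count.** Null data were simulated for 243 versus 81 with bivariate normal baseline and follow-up values (40,000 runs for each r). Each test alone rejected in about 5% of runs. Taking the smaller of the two p values gave 7.7%, 7.2%, 6.8% and 5.9% at r = 0.3, 0.5, 0.7 and 0.9. This covers one measure and two tests; adding regressions with freely chosen covariates cannot lower it.

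**The case against.** The strongest reply is that the sentence is a generic list, not a set of competing primary analyses. It spans between-group and within-group comparisons and all outcomes, the t tests may be meant for the within-group part, ANCOVA is already on it, and list order sets no priority. A journal article may also leave the covariate list to the full protocol or the SAP, neither of which is shown. Much of this stands: the missing covariates alone would not be a finding. What remains is that the sentence assigns the methods expressly to the primary outcome and none is named as deciding. The simple remedy uses a method the plan already lists.

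Four stronger readings are tempting, and the document does not support them.

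- *The trial is underpowered or has lost power.* A reader might infer this from the low t test figures under reading B. But the stated power reproduces without adjustment. The change-score t test falls below 0.80 only if 0.36 is in level SDs and r is below 0.5. The ratio 17% / 0.36 implies an SD of 47% of whatever the 17% is relative to. That may suggest a between-person SD, but the article does not say so, and the outcome is defined as a change.
- *ANCOVA always brings a large gain.* It shrinks as r rises: 2 points under reading A and none under reading B at r = 0.9.
- *Ignoring the strata makes the t test badly conservative.* Its actual size is about 2(1 − Φ(1.96/√(1 − R²))), where R² is the share of outcome variance explained by the strata. That gives 4.8%, 4.4% and 2.8% for R² of 2%, 5% and 20%. The article gives no R². For a change score only variance in the change counts, and stable differences in level cancel. The direction is also conservative.
- *Naming one ANCOVA fully fixes the primary test.* It does not: Outcome measures lists three estimates of insulin sensitivity without ranking them.

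**Conclusion.** The point holds as an improvement that should be made, not as an error in the power calculation. The plan applies several methods to the primary outcome without naming the one that decides, and ties none to the baseline value or the stratification factors.

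Its size depends on quantities the article does not give. Over correlations of 0.3 to 0.9, choosing ANCOVA over a t test on change adds about 13 down to 2 points of power if 0.36 is in change SDs, and about 17 down to 0 points if it is in level SDs. ANCOVA was at least as powerful in every case tried, so the recommendation does not depend on which reading is right. Leaving both tests available puts type I error at about 6% to 8% on one measure, and only if the more favourable result is the one taken as decisive. All figures rest on two-sided alpha 0.05, equal variances at the two visits and the planned 243 and 81 analysed.

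**What to change.** State one primary analysis: an ANCOVA of the follow-up value on randomized arm, baseline value of the same measure on the same scale, age, sex and BMI, reporting the adjusted between-group difference with its 95% CI. Fix the form in which age and BMI enter before the data are examined. Label the t tests and any other regression models supportive.

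This does not change the outcome. In a linear model with the baseline value as covariate, the arm coefficient is identical whether the dependent variable is the follow-up value or the change.

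The cost is wording in the analysis plan and a few degrees of freedom out of 324. All covariates are already collected at baseline and no participants are added. Which of the three insulin-sensitivity estimates is primary has to be settled separately.

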### Ethics

Ethical approval for the study was obtained in July 2012 from the Dublin City University Research Ethics Committee (DCUREC/2012/080). Funding is provided through DEXLIFE, an EU FP7 project (grant agreement no: 279228). Written informed consent will be obtained from each participant. Participants are able to withdraw from the trial at any time. All information disclosed in the study will be kept confidential and participants will not be identifiable in any material published as part of the study in any way. All data are stored without any identifying details. At all stages of research, the data will be stored using a password-protected computer and a secure locked cabinet; and all correspondence between research team members will be conducted using secure email.

## Discussion

This clinical trial is being conducted as part of the DEXLIFE project (www.dexlife.eu). DEXLIFE is an EU funded project whose objective is to identify novel metabolomic and lipodomic biomarkers that predict progression towards type 2 diabetes mellitus and are responsive to lifestyle intervention in people at increased risk [2]. This will be achieved by identifying novel biomarkers in longitudinal cohorts of subjects who have progressed from normal glucose tolerance to diabetes and determining the biomarkers that are correlated with improved glucose tolerance following the 12 week lifestyle intervention described in this protocol.

## Trial status

Recruitment started September 2012 and is expected to be complete by September 2015.

## Abbreviations

ANCOVA: analysis of covariance
CONSORT: Consolidated Standard of Reporting Trials
